### 2.10. Ecological Momentary Assessment 

Digital monitoring will be carried out using the EMA methodology via the MEmind app. This app offers daily short questions that appear on the smartphone screen. Each day, a notification will appear with 2–4 random questions, which will appear at a random time during the day (from 9 a.m. to 9 p.m.) and which are part of a pool of 33 questions that make up the questionnaire. 

This questionnaire is based on the Salzburg Suicide Process Questionnaire (SSPQ) [41], the Patient Health Questionnaire-9 (PHQ-9) [42], the Positive and Negative Affect Schedule (PANA) [43], the Interpersonal Needs Questionnaire (INQ) [44], and previous EMA studies [45,46,47,48]. 

Questions will remain as a notification on the screen until they are answered. The application also has a free text field in which the participant can write comments on their status.

The EMA questions belong to six categories:Suicidality: 4 questions;Non-suicidal self-injury: 2 questions;Affect: 9 questions;Interpersonal experiences: 11 questions;Sleep: 4 questions;Apetite and eating: 3 questions.

The complete list of Ecological Momentary Assessment (EMA) questions can be found in Appendix A.

The digital safety plan is incorporated into the MEmind app and consists of a set of personalized coping strategies that the participant can use in the event of a suicidal crisis [20]. The original safety plan was designed by Stanley and Brown (2012) [20] and has been proven in several studies to decrease the risk of suicide [21]. 

It should be designed with the help of clinical staff. The safety plan will take advantage of smartphones by offering participants the ability to call loved ones, show relaxation videos, activate pre-recorded messages, link to websites with health resources, or connect the participant to emergency resources. During the first visit, the safety plan will be customized with the participant based on their personal preferences (e.g., by providing a list of emergency contacts or programming the app to trigger a song, image or video pre-selected by the participant).

The tabs of the safety plan are: 

The security plan consists of 7 tabs. In each tab, the patient can add text messages, voice messages, audios, photos, videos and links to websites.

The 7 tabs in the security plan are as follows:

1. Warning Signs—warning signs (thoughts, images, moods, situations, behaviors, etc.…) that may indicate a crisis is occurring.

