2. Internal coping strategies—suggestions for distracting activities that participants can do on their own or without contacting another person (relaxation techniques, physical activityEtc.).

3. External coping strategies—suggestions for distracting activities that can be achieved with the help of the social environment.

4. Personal contacts—list of people in the participant’s support network. Only contacts can be added.

5. Professional contacts—professionals or institutions to contact during a crisis.

6. Safe environment—recommendations for making the environment safe.

7. Reasons for living—an important reason why life is worth living. For example, the participant could include a photograph (see Figure 2).

Apart from configuring the safety plan according to the individual needs of each participant, these tabs can be adapted to both the prevention of a suicide attempt and the prevention of self-harm. Thus, the warning signs can refer to both signs of an impending self-harm crisis and a suicidal crisis, while the safe environment can refer to both lethal-free and sharps-free, depending on the needs of each participant at each point in his or her evolution. The safety plan is multipurpose and can be tailored to each participant’s personal circumstances, providing a customized intervention. In addition, pre-loaded recommendations specific to NSSIs are included in the plan (explained below).

The different tabs contained in the MEmind safety plan are shown in Figure 3. 

Module of recommendations for the management of an NSSI crisis

In addition, the MEmind app includes a set of pre-installed recommendations for managing an NSSI crisis designed for young people. These recommendations include sections on ‘Identifying triggers’, ‘Strategies to use’, ‘Relaxing the five senses’ and ‘Stop’ (a series of intense stimuli that can act as a substitute for self-harm). 

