### 2.11. Assessments: Questionnaires 

The assessments will be conducted by psychologists and/or psychiatrists, except for the screening in schools, which will be self-administered and carried out by the participant. All questionnaires will be completed in the MEmind collection portal, which allows for easy completion and immediate uploading to databases. 

The screening will consist of the completion of the following two short scales: Paykel Suicide Risk Scale [36];Inventory of Statements about Self-Injury scale (ISAS) [37].

The following questionnaires and instruments will be used for the assessment of items related to suicidal behavior and suicide ideation:Sociodemographic data including gender, age, family socioeconomic status, grade repetition, sexual orientation, number of siblings (including the participant) and child adoption.The Columbia Suicide Severity Rating Scale (CSSRS) [34] will be administered to measure suicide ideation and behavior. This scale will be employed both in the basal and the follow-up appointments.In addition, we will verify suicide attempts and suicide deaths through the digital medical record (clinical events).The Inventory for Depressive Symptomatology—Clinical (IDSC-30) scale [49] will be administered in order to measure depressive signs and symptoms.MacLean Screening Instrument for Borderline Personality Disorder [50].The Spanish version of the Death/Suicide Implicit Association Test (D/S-IAT) [38]Satisfaction surveys (one qualitative and one quantitative satisfaction survey).

The quantitative survey consists of the following questions, which participants will rate from 1 to 10:

1. Please rate your overall satisfaction with the application.

2. Is the application easy to use? 

3. Is the performance of the application good (speed of navigation, accuracy, lack of errors...)?

4. How do you rate the quality of the graphics?

5. How secure is the application with regard to the processing of personal data?

6. To what extent does the application have a clinical benefit? 

7. Would you be willing to recommend this application to family or friends?

The qualitative survey will ask the participant to comment on how their participation in the project has been, what aspect they liked most, what aspect they liked least and what suggestions they have for improvement, as well as any additional comments they may wish to make. 

Both surveys will be carried out at the six-month visit. 

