### 2.12. Assessment Criteria

After six months, a before-and-after comparison will be made in both the control and intervention groups. 

Our main outcome will be a reduction in suicidal behavior, as measured by a score on the CSSRS.

Our secondary outcomes will be as follows: The occurrence of suicidal behavior as a clinical event (completed suicide, attempted suicide, ED visit for suicidal ideation, ED visit for self-harm),Predictive validity of the D/S IAT and SI IAT tests to clinical events recorded during follow-up.Acceptability of the project through user-perceived satisfaction.Project feasibility measured by participation and retention.

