### 2.13. Statistical Analysis

Traditional statistical analyses will be performed using SPSS 25.0 statistical software. For continuous variables, we will use t-tests to compare means between groups and ANOVA for multiple group comparisons. For categorical outcomes, chi-square tests will be employed to examine the frequency distributions.

In order to compare suicidal behavior (CSSRS score) at baseline and at the end of follow-up, a Wilcoxon test will be used. Survival curves (time to a new event, defined as a completed suicide, a suicide attempt or a visit to the emergency room for suicidal ideation) will be calculated using the Kaplan–Meier actuarial method.

To assess the feasibility of the project, the participation rate and retention (by percentage and by survival curve using drop-out as an event) will be calculated. To assess the acceptability of the project, descriptive statistics will be provided for the quantitative satisfaction survey and a content analysis will be conducted for the qualitative satisfaction survey. Binary logistic regression will be used to explore the correlation between the study variables, obtaining crude ORs adjusted for age and sex. 

Additionally, to reduce the probability of bias, we will factor by certain variables that could potentially act as confounders, such as the presence of other health apps in the users’ phones and response latency (which will be measured). 

All tests will be two-tailed, with a significance level of *p* < 0.05 and 95% confidence intervals.

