## 4. Expected Results

This project is highly feasible, as the mobile application it uses has already been tested in previous studies in the adult population [35]. With this intervention, we hope to contribute to the mental health of the adolescent population in the following two ways: Firstly, by decreasing suicidal behavior over the course of follow-up, i.e., both suicidal ideation and suicide attempts, which will be reflected in lower CSSRS scores in the intervention group. Secondly, by reducing NSSIs through the acquisition of coping strategies that can be used in times of risk. This training should be a useful tool beyond the follow-up period of the study and could be applied in the long term. As NSSIs increase the risk of a subsequent suicide attempt, it is hoped that reducing NSSI episodes will also reduce suicide risk.

We also expect that The D/S IAT and SI IAT will demonstrate predictive validity with respect to the gold standard CSSRS.

Finally, we also expect the project to be well accepted by the participants, which will be reflected in the satisfaction surveys provided. Demonstrating its feasibility will allow it to be implemented on a large scale.

Monitoring will be a source of information for understanding suicidal behavior, NSSIs and their associated factors. Real-time monitoring will facilitate an individualized approach that will allow for the design of prevention strategies tailored to the uniqueness of each patient. 

Finally, it is important to stress the importance of transmitting to the adolescent population the need to seek help if they find themselves in a situation of suicidal risk. Given that this is a population that integrates mobile devices into their daily lives, it is expected that the demand for help will be more accessible; it is also hoped that the reception of the preventive approach will be improved.

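### The clinical-event outcome has four components in section 2.12 but three in section 2.13, and one shared component, ED visits for suicidal ideation, may partly reflect help-seeking

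*Protocol article*

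**What the plan says.** Section 2.12 (Assessment Criteria) names the occurrence of suicidal behaviour as a clinical event as a secondary outcome and lists its contents: "completed suicide, attempted suicide, ED visit for suicidal ideation, ED visit for self-harm".

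Section 2.13 (Statistical Analysis) plans Kaplan–Meier curves for time to a new event, "defined as a completed suicide, a suicide attempt or a visit to the emergency room for suicidal ideation".

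Section 2.11 uses the term clinical events a third time, for the record check: "we will verify suicide attempts and suicide deaths through the digital medical record (clinical events"). ED visits are not named there.

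On the intervention, section 2.10 says the digital safety plan can "connect the participant to emergency resources" and describes one of its seven tabs as "professionals or institutions to contact during a crisis". Sections 2.1 and 2.7 give the plan to the intervention group only. Section 4 stresses "the need to seek help if they find themselves in a situation of suicidal risk" and adds that "it is expected that the demand for help will be more accessible".

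**The concern.** Two things are at stake.

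First, the lists differ by one component, and it bears directly on self-injury. The main objective in section 1 covers both suicidal behaviour and non-suicidal self-injury. Cohort 1 can enter on self-injury alone and is partly recruited in emergency departments (section 2.2.1). Leaving ED visits for self-harm out of the survival analysis removes its only item named for self-harm. A visit for self-harm without suicidal intent would count under section 2.12 and not under section 2.13, so the two analyses could disagree for reasons of definition alone.

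Second, an ED visit for ideation can mean deterioration, or it can mean that a participant in crisis sought help. One arm alone has a tool that eases contact with such help. If the visits are only pooled with attempts and deaths, a rise in help-seeking could offset a fall in attempts, and the reader could not see it.

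**Working it through.** **Step 1: the lists side by side.**

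| Event | 2.11 record check | 2.12 secondary outcome | 2.13 survival event |
|---|---|---|---|
| Suicide | named | yes | yes |
| Suicide attempt | named | yes | yes |
| ED visit, suicidal ideation | not named | yes | yes |
| ED visit, self-harm | not named | yes | **no** |

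The 2.12 list minus the 2.13 list is exactly one item, the ED visit for self-harm. No section explains the difference or presents the two lists as separate endpoints. Section 2.12 does not list time to event as an outcome of its own.

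**Step 2: is there a figure in the plan to reproduce?** No. The sample size in section 2.3 rests on a standardised effect of 0.5. No event rate, risk ratio or hazard ratio is given for clinical events, so what follows is illustration only.

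**Step 3: what the definitions could do, under assumed rates.** Assumptions, none from the documents:
- Control six-month risks are 10% for suicide or attempt, 10% for ED visit for ideation and 5% for ED visit for self-harm.
- The plan multiplies attempts and self-harm visits by 0.7, and ideation visits by k.
- Components are added, which ignores participants with more than one event.

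Three-part risk ratio = (7 + 10k) / 20. Four-part risk ratio = (7 + 10k + 3.5) / 25.

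| k | Three-part (2.13) | Four-part (2.12) |
|---|---|---|
| 0.7 | 14/20 = 0.70 | 17.5/25 = 0.70 |
| 1.0 | 17/20 = 0.85 | 20.5/25 = 0.82 |
| 1.3 | 20/20 = 1.00 | 23.5/25 = 0.94 |
| 1.5 | 22/20 = 1.10 | 25.5/25 = 1.02 |

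With control risks of 5% or 10% for attempts, 5% or 10% for ideation visits, and 0 or 5% for self-harm visits, the ratio at k = 1.5 runs from 0.90 (18/20, from 10%, 5%, 5%) to 1.23 (18.5/15, from 5%, 10%, 0). At k = 0.7 it is 0.70 throughout. The sign of the distortion depends on k, which is unknown.

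**Step 4: would suicide or attempt alone be the better headline?** Take 1080/2 = 540 per arm, no dropout, two-sided 5%:

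power = Φ{ [ |p₁ − p₂| − 1.96·√(2p̄(1 − p̄)/n) ] / √(p₁(1 − p₁)/n + p₂(1 − p₂)/n) }

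- Suicide or attempt only, 10% v 7%: (0.03 − 1.96 × 0.01697)/0.01695 = −0.19, power about 42%.
- Three-part composite, k = 0.7, 20% v 14%: (0.06 − 1.96 × 0.02286)/0.02279 = 0.67, power about 75%.
- Three-part composite, k = 1.0, 20% v 17%: (0.03 − 1.96 × 0.02363)/0.02361 = −0.69, power about 24%.

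The narrower outcome does better if ideation visits do not fall and worse if they fall as much as attempts. This is a trade-off, not a reason to replace the composite.

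**The case against.** The best defence is that each list belongs to its own use: the four-part list to occurrence, the three-part list to the curves. The curves may be meant for suicidal events only, and section 2.10 does separate self-harm crises from suicidal crises. That reading is possible, but the article does not state it, so the difference still has to be reconciled.

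On help-seeking, the defence has more force. Emergency connection is one function among several, and most of the seven tabs concern warning signs, coping, a safe environment and reasons for living. Section 4 expects help to become more accessible but does not predict more ED visits, and it also expects ideation itself to fall, so these visits might fall. Section 2.12 never calls its list a composite, so separate reporting is not excluded. What remains is a caution about interpretation.

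Three further inferences are tempting and are not supported:
- That the mismatch changes the criterion for the implicit association tests. Section 2.12 ties their predictive validity to recorded clinical events, and the three-part list is attached only to the survival curves.
- That the lack of a named between-arm test for the curves is a defect. A condensed article may leave this to an analysis plan that is not shown.
- That the safety plan is built to produce the visits scored as failure. This overstates sections 2.10 and 4.

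**Conclusion.** The mismatch is literal and stands: four components in section 2.12, three in section 2.13, with ED visits for self-harm omitted without explanation although self-injury is part of the main objective. It is confined to a secondary outcome; the CSSRS main outcome is untouched.

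The second part stands only as a possibility. ED visits for ideation could rise in the intervention arm while suicidal behaviour falls, and the article plans no stated separation of the two. A reader might infer from the row at k = 1.3 that the composite would hide a real benefit entirely. That exact cancellation comes from choosing equal control risks and equal and opposite 30% changes. With no event rates in the documents, the figures show how the definitions can diverge and do not estimate a bias.

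**What to change.** - Use one event list in sections 2.12 and 2.13, including ED visits for self-harm.
- Align section 2.11 so that the medical-record check covers every listed event. It now names only attempts and deaths, so it is not confirmed that ED visits are captured from the same source.
- Alongside the composite, report by arm: suicide or attempt; ED visit for self-harm; ED visit for suicidal ideation. State in advance that the last may partly reflect help-seeking, so a difference in either direction should be read with caution.

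The composite can stay as the headline for this secondary outcome.

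The cost is mostly wording, with a little more analysis and reporting. The component estimates will be imprecise: step 4 gives about 42% power for suicide or attempt alone under its assumptions. If the record check does not yet cover ED visits, extending it adds some data-collection work.

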### 2.7. Randomization and Follow-Up

A 1:1 randomization will take place after enrollment, where each participant will be assigned to one of the two groups. In both the control and intervention groups, an initial visit will take place during which a psychiatrist or psychologist will install the MEmind app on the participants’ mobile phone so that they can answer the questionnaires contained in the app with the guidance of the evaluator. In the case of self-administered questionnaires, the participants will answer directly on the screen of their mobile phone. In the case of hetero-administered questionnaires, the evaluator will complete them via the MEmind web portal, which is synchronized with the application.

Participants will be followed for six months, with weekly and monthly telephone visits and face-to-face visits at three and six months. In the intervention group, participants will also be given access to the safety plan included in the MEmind application. During the baseline visit, the plan will be set up for the first time and how it works will be explained. 

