### 2.9. Implicit Association Test

The Spanish versions of the SI-AT and D/S-IAT [39] will be administered. These are 5 min tests administered by computer. The D-S IAT requires participants to match words from the following two semantic fields: “death” (die, dead, deceased, lifeless, and suicide) and “life” (alive, survive, live, thrive, and breathing). The attributes “me” (I, myself, my, self, and mine) and “not me” (they, them, their, theirs, and other) are used to categorize the words. The reaction times are processed using the standard D algorithm for IATs [40]. The algorithm takes into account the reaction time for the implicit association with death (faster reaction scores positively) and the reaction time for the implicit association with life (faster reaction scores negatively). Therefore, a participant with an unconscious bias towards life will have a negative score and a person with an unconscious bias towards death will have a positive score. The greater the score, the stronger the association in one direction or the other. A similar principle is applied for the SI-IAT, albeit using semantic fields related to self-harm. 

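### Response latency is listed as a confounder to adjust for, but on the natural reading it arises after randomisation, so adjusting a between-arm effectiveness analysis for it can bias the estimate

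*Protocol article*

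**What the plan says.** Section 2.13 of the protocol article states, as a measure against bias, that "we will factor by certain variables that could potentially act as confounders". It names two: other health apps on the participant's phone, "and response latency (which will be measured"). It does not say how latency is defined, when it is recorded, or which analysis the factoring belongs to.

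Three other sections bear on what latency can be:

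- Section 2.7 (Randomization and Follow-Up) says: "A 1:1 randomization will take place after enrollment, where each participant will be assigned to one of the two groups". It then continues: "In both the control and intervention groups, an initial visit will take place during which a psychiatrist or psychologist will install the MEmind app". Installation is thus described after allocation and by allocated group.
- Section 2.10 (Ecological Momentary Assessment, EMA) has the app issue short questions every day at a random time, and adds: "Questions will remain as a notification on the screen until they are answered". This yields a time from prompt to answer.
- Section 2.10 also says: "The digital safety plan is incorporated into the MEmind app". By sections 2.1 and 2.7, both arms receive the EMA, but only the intervention arm receives the safety plan.

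Section 2.9 describes one other response time, that of the Implicit Association Tests: "The reaction times are processed using the standard D algorithm for IATs".

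Section 3 (Limitations) separately mentions covariance analysis for baseline differences and an intention-to-treat analysis. It does not mention latency.

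**The concern.** A confounder of a randomised comparison would have to influence which arm a participant is in. A variable that comes into being after allocation cannot do so. If treatment can change it, conditioning on it does not protect the comparison and may damage it, in two ways:

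- **Mediator.** The safety plan gives one arm an extra reason to open the app and may change how quickly prompts are answered. If answering speed or engagement in turn affects suicidal behaviour, holding latency constant takes that part of the effect out of the estimate.
- **Shared cause.** Distress may affect both how quickly a participant answers and the score on the Columbia scale (CSSRS). If treatment also shifts latency, participants with equal latency in the two arms differ in distress. A difference can then appear where there is none, or a real one can be distorted.

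Stratifying by latency and entering it as a covariate share this problem, so the vagueness of factoring does not avoid it. At stake is a step offered as bias reduction that could work the other way, in a comparison that randomisation and the intention-to-treat analysis of section 3 are meant to protect.

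**Working it through.** **Timing.** Setting sections 2.7 and 2.10 side by side gives this order: enrolment, 1:1 allocation, initial visit with app installation (and safety plan set-up in the intervention arm), then daily prompts. EMA latency is observed only at the last step. Nothing in the article limits it to a value taken before allocation.

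**Size.** The plan gives no figure for latency, so there is none to reproduce. The one figure borrowed from it is the effect size of 0.5 in section 2.3. That figure comes from a one-sample calculation, so using it as a between-arm standardised difference is itself an assumption.

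Take a linear model in SD units, with latency scaled to unit variance within arm:

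- a = shift in latency caused by the safety plan
- m = effect of latency on the outcome
- b, g = loadings of an unmeasured common cause (distress) on latency and on the outcome

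Within arm, the slope of outcome on latency is s = m + b × g. The estimate with latency in the model is

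adjusted effect = total effect − a × s.

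The bias is therefore a × s in size. It is zero if a = 0 (treatment does not move latency) or if s = 0 (latency neither affects the outcome nor shares a cause with it).

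*Mediator case (b × g = 0, so s = m), all inputs assumed, with a × s in the direction of benefit:*

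| Shift a | Slope s | a × s | Left of 0.25 | Lost | Left of 0.5 | Lost |
|---|---|---|---|---|---|---|
| 0.1 | 0.2 | 0.02 | 0.23 | 8% | 0.48 | 4% |
| 0.1 | 0.4 | 0.04 | 0.21 | 16% | 0.46 | 8% |
| 0.5 | 0.2 | 0.10 | 0.15 | 40% | 0.40 | 20% |
| 0.5 | 0.4 | 0.20 | 0.05 | 80% | 0.30 | 40% |

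*Check by simulation* (1,000,000 participants, 1:1, least squares). Negative values mean benefit, and the assumed shift is −0.2 or −0.5:

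| Assumed paths | s | Shift | Formula, true 0 | Simulated, true 0 | Formula, true −0.50 | Simulated, true −0.50 |
|---|---|---|---|---|---|---|
| b = g = 0.5, m = 0 | 0.25 | −0.2 | +0.05 | +0.050 | −0.45 | −0.450 |
| b = g = 0.5, m = 0.2 | 0.45 | −0.2 | +0.09 | +0.090 | −0.41 | −0.410 |
| b = g = 0, m = 0.4 | 0.40 | −0.2 | +0.08 | +0.079 | −0.42 | −0.421 |
| b = g = 0.5, m = 0 | 0.25 | −0.5 | +0.125 | +0.126 | −0.375 | −0.374 |
| b = g = 0.5, m = 0.2 | 0.45 | −0.5 | +0.225 | +0.226 | −0.275 | −0.274 |
| b = g = 0, m = 0.4 | 0.40 | −0.5 | +0.20 | +0.199 | −0.30 | −0.301 |

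Without latency in the model, every scenario returned the true total effect to within 0.001. With no shift in latency, or with s = 0, the adjusted estimate was also within 0.001 of the truth.

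The direction is not fixed. If a × s has the opposite sign to the true effect, the same formula gives an exaggerated effect rather than a diluted one.

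**The case against.** A reader might infer that the trial's main result will be biased. The article does not support that, for these reasons:

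- **The target analysis is not named.** The effectiveness methods in section 2.13 (t-tests, chi-square, the Wilcoxon test of baseline against end of follow-up, Kaplan–Meier curves) carry no covariates. The factoring sentence follows, in a new paragraph, a logistic regression meant to explore associations among the study variables. It could be confined to that work. For an association that is not a treatment effect, such as test scores against clinical events, latency could be a reasonable covariate. This stands as a limit on the point. It does not remove it: the sentence is general, sits in the overall analysis section, and speaks of confounders and bias.
- **Latency is undefined.** It could mean reaction time in the Implicit Association Tests. A test taken at baseline before the safety plan is shown could hardly be affected by it. That reading is possible but less natural, and the text does not restrict latency to it.
- **No effect of treatment on latency is stated.** Both arms answer the same prompts in the same app. If the safety plan leaves latency unchanged, adjustment does no harm. This stands, and it is why the conclusion is that adjustment can bias, not that it does.
- **The sizes are assumed.** This also stands. They illustrate the mechanism and predict nothing for this trial.

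A reader might also extend the point to other health apps. The article does not say when these are recorded. Recorded at enrolment, they are a legitimate covariate, and the timing is a detail that an article may leave to the full protocol.

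Leaving the whole matter to the analysis plan is not an answer, because the article already names latency as an adjustment variable and a plan written from it would carry the problem forward.

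**Conclusion.** The point holds in conditional form. On the natural reading, response latency is recorded after randomisation in an app whose content differs by arm, so it is not a confounder of the randomised comparison. Used in a between-arm effectiveness analysis, it can bias the estimate by the product of the latency shift and the within-arm slope. Under the assumed inputs that product is 0.02 to 0.20 SD in the mediator case, and up to about 0.23 SD in the scenarios that add a shared cause. The conclusion rests on two readings that the article does not settle: that latency means EMA prompt latency, and that the factoring reaches the comparison of arms. It also needs the safety plan to change latency, and latency to affect the outcome or share a cause with it. The wording should be corrected because it labels such a variable a confounder and sets no limit on its use.

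**What to change.** Amend the sentence in section 2.13 so that covariates or strata in between-arm effectiveness analyses are limited to variables fixed before randomisation, for example baseline CSSRS, centre or cohort, age, sex, and other health apps as recorded at enrolment. Remove response latency from that set. State what latency measures, and report it by arm as an engagement measure or in an analysis labelled exploratory.

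The cost is one sentence of text. Latency can still be collected as planned, and recruitment and sample size are unaffected.
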